# A single-center, prospective, randomized clinical trial to investigate the optimal removal time of the urinary catheter after laparoscopic anterior resection of the rectum: study protocol for a randomized controlled trial

**DOI:** 10.1186/s13063-019-3210-1

**Published:** 2019-02-15

**Keywords:** Removal time, Urinary catheter, Acute urinary retention, Urinary tract infection, Laparoscopic anterior resection of the rectum

## Abstract

**Background:**

Urinary catheter placement is essential before laparoscopic anterior resection for rectal cancer. Whether early removal of the catheter increases the incidence of urinary retention and urinary tract infection (UTI) is not clear. This study aims to determine the optimal time for removal of the urinary catheter after laparoscopic anterior resection of the rectum.

**Methods/design:**

A total of 220 participants meeting the inclusion criteria will be randomly assigned to an experimental group or a control group. The experimental group will have their urethral catheters removed on postoperative day 2 and the control group will have their urethral catheters removed on postoperative day 7. In both groups, catheter removal will be performed when the bladder is full. The incidence of urinary retention and UTI in the two groups will be compared to determine the optimal catheter removal time.

**Discussion:**

This is a prospective, single-center, randomized controlled trial to determine whether early removal of the urinary catheter after laparoscopic anterior resection of the rectum will help to decrease the incidence of postoperative acute urinary retention and UTI.

**Trial registration:**

ClinicalTrials.gov, NCT03065855. Registered on 23 February 2017.

**Electronic supplementary material:**

The online version of this article (10.1186/s13063-019-3210-1) contains supplementary material, which is available to authorized users.

## Background

A urinary catheter is routinely placed before abdominal surgery to allow good visualization of the operative field. The catheter helps to avoid accidental trauma to the bladder and facilitates monitoring of kidney function during and after surgery. It is especially useful during anterior resection of the rectum because of the high risk of nerve injuries that could result in urinary retention or bladder dysfunction. The time for removal of the catheter varies in different operations. Traditionally, the catheter is retained for 7 days because early removal of the urinary catheter is reported to be associated with a higher incidence of urinary retention.

Generally, the longer the catheter is retained, the higher the risk of urinary tract infection (UTI). The recent Enhanced Recovery After Surgery (ERAS) guideline, taking into account the discomfort and anxiety suffered by patients, recommends that urinary catheters placed via the urethra be withdrawn 48 h after colon/rectal surgery in patients receiving epidural pain relief [1]. However, the literature referenced in the guideline mainly included patients undergoing colorectal surgery and not anterior resection of the rectum, which is the focus of our research. Most authors still believe that a longer time of indwelling catheterization can reduce the possibility of acute urinary retention and long-term bladder dysfunction.

During our review of the literature we found only one randomized controlled trial (published in 1999) indicating that early removal of the catheter was associated with higher risk of urinary retention [2]. Recent studies have reported contradictory results, with some authors claiming that early removal of the urinary catheter increases the risk of urinary retention [3] and others claiming the opposite [4]. Advances in laparoscopic techniques have made it possible to clearly visualize and preserve the superior hypogastric nerve and the pelvic nerve (which are associated with urinary function) during radical surgery. In addition, with the introduction of dissection along the embryonic plane and the use of neoadjuvant therapy for tumor reduction, protection of the nerves has become easier.

The purpose of this prospective, randomized controlled study is to compare the incidences of acute urinary retention and UTI in patients having catheter removal at 2 days and 7 days after laparoscopic anterior resection and thus establish the optimal time for catheter removal. The primary outcome measure is the incidence of urinary retention. The secondary outcome measures are the incidence of UTI, time of off-bed activity, and subjective discomfort. The study protocol has been written in accordance with the Standard Protocol Items: Recommendations for Interventional Trials (SPIRIT) checklist (Additional file 1).

## Methods

### Study design

This study is a superiority trial and is designed as a prospective, single-center, randomized, parallel-group, single-blind, clinical controlled study. Rectal cancer patients will be enrolled and divided into two groups: the early removal group (the intervention group) and the normal removal group (the control group). The flow diagram for this trial is shown in Fig. 1.

**Fig. 1 Fig1:**
[figure not shown]
Flow diagram of enrollment, intervention, and assessment. IPSS International Prostate Symptom Score

The sample size was estimated as follows. According to the latest studies, the incidence of urinary retention after rectal surgery is 25% when the catheter is removed within 2 days after surgery and 10% when the catheter is removed after 7 days. To detect these outcomes with *α* = 0.05 and *β* = 0.2, we would need 100 patients per group (total 200). We decided to enroll 110 patients in each group (total 220), to allow for a possible 10% dropout rate.

### Outcome measures

#### Primary outcome measures

Postoperative urinary retention requiring recatheterization following urethral catheter removal.

Acute postoperative urinary retention is defined as > 100 ml postvoid residual urine demonstrated on bladder ultrasound, with need for recatheterization within 1 day of removal of the urethral catheter [2].

#### Secondary outcome measures

Urinary tract infection occurring following urethral catheter removal.

A midstream urine sample will be taken for microscopy and culture before catheter removal. A urinary leukocyte count ≥ 5 per high-power field for men and ≥ 1 per high-power field for women will be considered as bacteriuria, irrespective of whether or not symptoms of urinary irritation are present. A pure culture of a single organism of > 100,000 colony forming units will be considered a positive culture [2].(2)Urethrorrhagia following urethral catheter removal.

The presence of ≥ 3 red blood cells (RBC) per high-power field will be recorded as urethrorrhagia [2].(3)Anxiety score before operation and on postoperative day 4.

The Zung Self-Rating Anxiety Scale will be used to assess anxiety levels. This is a standard scale for measurement of anxiety, and is mainly used to assess the efficacy of treatments [5].

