### Detailed description of procedure

Catheterization will be performed using all aseptic precautions. The investigator will ensure that the drainage bag is positioned intraoperatively and postoperatively. The drainage tube ends and drainage bags will not be higher than the pubic symphysis, and will be kept unobstructed. The urethra, urethral orifice, and perineum will be kept clean when removing the catheter so that a clean midstream urine sample can be collected for urine routine examination and culture. The catheter retention duration will be recorded, and also the first self-urination time, residual urine, pain score, and recatheterization (if any).

For all patients the catheter will be clamped for some time so that the bladder is full when the catheter is removed. The catheter will be pulled out when the desire for urination is at a peak and bladder pressure is increasing. These measures are conducive to the recovery of bladder function and establishment of an effective micturition reflex, which can effectively shorten the time to first micturition after catheter removal.

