## Discussion

Most researchers still believe that longer retention of the urinary catheter after surgery reduces the incidence of acute urinary retention and bladder dysfunction [6]. Early catheter removal and resulting urinary retention leads to recatheterization and, thus, to higher risk of UTI. However, overlong retention of the catheter has been shown to cause permanent injury to the detrusor in animal experiments [7].

Urinary retention refers to an inability to completely empty the bladder. Despite a large amount of collected urine, the patient will not have the desire to micturate. Several factors contribute to the occurrence of urinary retention, including surgical trauma, the procedure of catheter removal, and prolonged catheterization.

Damage to nerve fibers from S3–S4 spinal segments during rectal surgery could lead to detrusor dysfunction and urinary retention [8]. This is most commonly reported after low anterior resection (LAR; 15–25%), abdominoperineal resection (APR; ~ 50%), and laparoscopic surgery [9]. Deeper anesthesia and longer duration of surgery are also associated with a delay in recovery of the micturition reflex [10]. Anxiety also leads to a delay in the recovery of bladder function.

The procedure of catheter removal is very important. Clinical trials show that the catheter is ideally removed when the bladder is distended. The increased bladder pressure helps the detrusor contract strongly after catheter removal, and this facilitates recovery of the micturition reflex. Therefore, in this study all investigators will undergo training to standardize the procedure of catheter removal. Prolonged catheterization leads to loss of bladder smooth muscle tone, which may also lead to bladder sphincter dysfunction [11]. In addition, prolonged catheter retention irritates the urethral mucosa and causes inflammatory reaction and edema. All of these factors contribute to the occurrence of urinary retention.

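### The UTI outcome is meant to follow catheter removal but its urine sample is set before removal, and the plan does not say whether leukocytes, culture or both make a UTI

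*Protocol article*

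**What the plan says.** The Protocol article, under Secondary outcome measures, lists "Urinary tract infection occurring following urethral catheter removal". The sampling rule that follows is: "A midstream urine sample will be taken for microscopy and culture before catheter removal".

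Two laboratory criteria are then given. The first is "A urinary leukocyte count ≥ 5 per high-power field for men and ≥ 1 per high-power field for women will be considered as bacteriuria", and it applies "irrespective of whether or not symptoms of urinary irritation are present". The second is "A pure culture of a single organism of > 100,000 colony forming units will be considered a positive culture". No sentence says which of them, alone or together, makes a UTI.

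Under Detailed description of procedure the timing differs: the urethra and perineum are to be "kept clean when removing the catheter so that a clean midstream urine sample can be collected" for routine examination and culture. Under Grouping, removal is on postoperative day 2 in the experimental arm and day 7 in the control arm.

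UTI is the first secondary outcome listed in the Background, and the stated purpose names it beside retention. The Discussion gives a route by which early removal could raise it: "Early catheter removal and resulting urinary retention leads to recatheterization and, thus, to higher risk of UTI".

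**The concern.** The outcome and its measurement refer to different periods. A specimen obtained while the catheter is in place describes the catheter period; it says nothing about infection after removal. The word midstream does not fit either, because a midstream specimen is a voided one.

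Tying the sample to removal also means that the two arms are examined at different times since surgery and after different catheter exposure. Infection that starts later in the early arm, including after recatheterisation, has no described sample that would find it.

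Separately, leukocytes are white cells, not bacteria. Without a rule linking the leukocyte count to the culture result, two analysts could report different UTI rates from the same data.

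The removal time is to be judged on retention and UTI together, so an unclear UTI rate weakens half of that comparison.

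**Working it through.** **1. Timing, side by side.**

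| Place in the Protocol article | Time implied |
|---|---|
| Outcome label (Secondary outcome measures) | after removal |
| Sampling sentence (Secondary outcome measures) | before removal |
| Specimen type, midstream (both sections) | a void, so not with the catheter draining |
| Detailed description of procedure | at removal |

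The sampling sentence disagrees with the other three. Whether the sample is taken before or at removal, it falls on day 2 in one arm and day 7 in the other.

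**2. Definition.** A patient with leukocytes above the limit and a negative culture is a UTI case if either criterion suffices, and not a case if culture or both are required. The text does not choose.

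**3. The plan's own figure.** The article gives no sample size for UTI. For retention (25% vs 10%, two-sided alpha 0.05, power 0.80, mean rate 0.175):

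n = [1.96 × √(2 × 0.175 × 0.825) + 0.842 × √(0.25 × 0.75 + 0.10 × 0.90)]² / 0.15² = (1.053 + 0.444)² / 0.0225 ≈ 99.6, so 100 per group. The stated figure reproduces. Since the primary outcome requires recatheterisation, 25% and 10% are also the planned recatheterisation rates.

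**4. Infections after recatheterisation that a sample at removal would not count.** Let q be the share of recatheterised patients who become infected. The documents give no value, so q is an assumption. Uncounted infections per 100 patients are 25 × q (early) and 10 × q (control); the difference is 15 × q.

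| q | Early | Control | Difference (points) |
|---|---|---|---|
| 10% | 2.5 | 1.0 | 1.5 |
| 20% | 5.0 | 2.0 | 3.0 |
| 30% | 7.5 | 3.0 | 4.5 |
| 50% | 12.5 | 5.0 | 7.5 |

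**5. Set against a UTI difference.** The Discussion cites an earlier randomised trial with UTI in 20% vs 42% (removal on day 1 vs day 5), a difference of −22 points. Take these, for illustration, as the rates at removal, and count only new infections in patients negative at that time. The early arm gains 0.80 × 0.25 × q and the control arm 0.58 × 0.10 × q. The full difference is −22 + 14.2 × q points: −20.6 (q = 10%), −19.2 (20%), −17.7 (30%), −14.9 (50%). The sign does not change.

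**6. The leukocyte rule.** If a share f of uninfected patients in both arms exceeds the leukocyte limit and is counted as UTI, the observed difference is −22 × (1 − f): −19.8 (f = 10%), −17.6 (20%), −15.4 (30%). Here too f is an assumption. With f = 20% the trial would observe −17.6 points, against a full difference of −17.7 at q = 30%. At these values the two effects nearly cancel.

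**The case against.** The strongest reply is that the timing sentence is a wording slip. The outcome label, the word midstream and the procedure section all point to collection at or after removal. That is plausible, but the sentence still has to be corrected, and the other reading still ties the sample to day 2 or day 7.

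A second reply is that the points in step 4 do not measure the mistimed sentence. They come from infection after recatheterisation, and moving the sample to the first void would still miss most of it. This stands: the size belongs to the lack of a later assessment. A reader might go on to infer that such infections are never sampled. The documents do not support that, because the flow diagram and the full protocol are not shown. What can be said is that the article describes no later sample.

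A reader might also infer that the UTI comparison is biased in favour of early removal. That is not shown. Uncounted infections would favour early removal, but the leukocyte rule dilutes a difference if pyuria without infection is equally common in both arms. Even that equality is uncertain, since the Discussion says that prolonged catheterisation inflames the urethral mucosa.

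Nor does the leukocyte rule cause infections to be missed; it over-counts. The timing problem should not be extended to the red-cell outcome, for which no sample time is given. Finally, a rule combining the two UTI criteria may exist in the full protocol, and a culture-only definition may be less comparable with the cited trial. Both are fair, but labelling a leukocyte count as bacteriuria is wrong as it stands.

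**Conclusion.** The point holds as a wrongly fixed secondary endpoint. The article contradicts itself on when the sample is taken, and its UTI definition cannot be applied in only one way. Followed literally, it measures urine findings during catheterisation at day 2 vs day 7, not the stated outcome.

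Uncounted infections after recatheterisation would fall 2.5 times as often in the early arm (25% vs 10%), an excess of 1.5 to 7.5 points. This assumes that 10% to 50% of recatheterised patients become infected, with the same risk in both arms, that all these infections are new, and that no later sample exists. The net direction of bias is not established.

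This should be fixed. It does not touch the primary outcome or the sample size.

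**What to change.** - Reconcile Secondary outcome measures with Detailed description of procedure, so that the sample is a clean midstream void after removal. State what specimen is used for patients who cannot void.
- Define UTI by the culture criterion already in the text (a single organism, more than 100,000 colony forming units). Report leukocyte counts separately as pyuria.
- Count UTI in both arms from surgery to one common postoperative cut-off, including culture-positive infections after recatheterisation. This step, not the move to the first void, closes the gap in step 4.

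The cost is revised wording, a urine sample at the common time point (recatheterised patients included), and fewer events qualifying as UTI, hence less precision for that comparison. If the full protocol already contains a later assessment or a combined definition, the article's text needs only to be aligned with it.

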### Participating centers and investigators

This will be a single-center study, with all patients enrolled from the Peking Union Medical College Hospital.

The surgeons participating in this study will have performed > 100 laparoscopic colorectal surgeries per year for 2 consecutive years and will have proven ability to complete the laparoscopic surgery procedure. Every investigator will participate in training on the correct technique for removal of urinary catheters.

### Ethical considerations

This trial protocol has been approved by the Ethics Committee of Peking Union Medical College Hospital (ZS-1269) and has been registered at Clinical-Trials.gov (identifier NCT03065855). All eligible participants and/or their legal surrogates will be fully informed of the potential risks and benefits of the interventions in each group. Only patients who provide written informed consent will be enrolled in the trial.

### Study subjects

The study participants will be rectal cancer patients requiring laparoscopic anterior resection of the rectum.

#### Inclusion criteria

Age 18–75 years.Diagnosed with rectal cancer and posted for total or tumor-specific mesorectal excision with colorectal or coloanal anastomosis.American Society of Anesthesiologists (ASA) classification of 1–3.

#### Exclusion criteria

Preoperatively diagnosed urinary tract infections or urinary system diseases (including end-stage renal disease, neurological bladder dysfunction, and malignancy).Previous history of urinary retention or of having received drugs likely to affect bladder function.Male patients with disease of the prostate (such as benign prostatic hyperplasia).Patients receiving emergency surgery.

#### Exit criteria

Rectal cancer surgery is combined with additional pelvic surgery (including pelvic lymph node dissection, hysterectomy, salpingo-oophorectomy, posterior vaginectomy, cystectomy, ureteral double-J stenting, ureterectomy, ureteroureterostomy, prostatectomy).There is significant intraoperative damage to the pelvic nerve (patients classified as type IV by the Sugihara standard).Postoperative Clavien–Dindo grade III or VI complications.

### Randomization and blinding

Patients will be randomized to the study group and the control group with an allocation ratio of 1:1. Randomization will be done using random numbers generated with Statistical Analysis System (SAS) software. A central randomization system will be employed. All of the researchers will register on the website of the research system. When a researcher has chosen a certain patient, he/she will log in to the webpage and upload the basic information on the patient. The group allotment will then be revealed.

All patients will be undergoing the same (similar) surgery. The only difference will be the catheter removal time. Obviously, it is impossible to blind the surgeons who will perform the operations. However, all surgeon researchers will be required to limit potential cointerventions as much as possible. Result assessment will be made by independent researchers blinded to the surgical procedures.

### Preoperative evaluation

Preoperative evaluation will include the following:Elicitation of history of previous urinary system disease.Evaluation of bladder function and residual urine by B-mode ultrasonography.Urine routine examination to confirm that there is no pre-existing urinary tract infection or hematuria.

### Grouping

All participants will undergo urethral catheter insertion after placement of the epidural catheter for analgesia. After urethral catheter placement the participants will be randomly assigned to either the experimental arm or the control arm.

Participants assigned to the experimental arm will have their urethral catheters removed on postoperative day 2, and participants assigned to the control group will have their urethral catheters removed on postoperative day 7. In both groups, catheter removal will be done when the bladder is distended; this is standard practice in our institution. Control group patients will practice intermittent catheter clamping from postoperative day 4 onward.

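### Randomisation appears to come before the resection although the arms do not differ until postoperative day 2, so two intraoperative exit criteria are judged after allocation

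*Protocol article*

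**What the plan says.** **Timing of randomisation.** Grouping says that the urethral catheter goes in after the epidural, and then: "After urethral catheter placement the participants will be randomly assigned to either the experimental arm or the control arm". The Abstract ("Urinary catheter placement is essential before laparoscopic anterior resection for rectal cancer") and the Background ("A urinary catheter is routinely placed before abdominal surgery to allow good visualization of the operative field") both place catheterisation before the operation. Under Randomization and blinding, the researcher enters the patient on a central website and the allotment is shown at that point.

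**Where the arms part.** Randomization and blinding describes the surgery as the same in both groups and adds: "The only difference will be the catheter removal time". The first arm-specific act is on day 2: "Participants assigned to the experimental arm will have their urethral catheters removed on postoperative day 2". The control arm's own step comes later: "Control group patients will practice intermittent catheter clamping from postoperative day 4 onward".

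**Exits.** Exit criteria lists additional pelvic surgery (with named procedures), then "There is significant intraoperative damage to the pelvic nerve (patients classified as type IV by the Sugihara standard", then postoperative Clavien–Dindo complications. The first two are established at operation.

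**Blinding.** "Obviously, it is impossible to blind the surgeons who will perform the operations". Surgeons are asked to limit cointerventions, and outcome assessment is by independent researchers blinded to the surgical procedures. Nothing says that the allocation is withheld from the operating team.

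**The concern.** Allocation is disclosed earlier than the design needs. Nothing done in theatre depends on the arm, yet on the natural reading the arm is already known, or can be known, while the patient is operated on and while the two intraoperative exit criteria are judged.

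The Discussion gives damage to the nerve fibres supplying the bladder as a cause of retention, so the nerve-damage exit removes patients at high risk of the primary outcome. The sample-size paragraph under Study design expects more retention after early removal (25% against 10%), so a team that knows the arm has an expectation that could influence dissection, nerve grading or the decision to exit a patient. If such exits differed by arm, the remaining groups would no longer be comparable on a strong predictor of retention.

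The stated reason for not blinding surgeons is also weaker than it sounds. It holds only because of when randomisation is done. If allocation followed surgery, the surgeon would be unaware of it throughout the operation.

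**Working it through.** **1. Sequence of events.** Put in order, the sections give: epidural; catheter; randomisation with disclosure; resection; determination of additional pelvic surgery and nerve damage; day 2, removal in the experimental arm; day 4, clamping begins in the control arm; day 7, removal in the control arm. The allocation is first needed at the day-2 step. Grouping does not say outright that randomisation precedes resection. The two statements that catheterisation is preoperative, and the listing of intraoperative findings as exits rather than exclusions, make that the natural reading.

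**2. The plan's own figure.** Inputs from Study design: p1 = 0.25, p2 = 0.10, α = 0.05, β = 0.2. Tests are two-sided (Statistical analysis). With mean p̄ = 0.175,

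n = [1.96·√(2·0.175·0.825) + 0.8416·√(0.25·0.75 + 0.10·0.90)]² / 0.15² = (1.0532 + 0.4434)² / 0.0225 ≈ 99.5, so 100 per group.

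The stated 100 is reproduced. The point does not rest on it.

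**3. What unequal exits could do.** No exit rate is given, so every input here is an assumption: the true retention risk p is the same in both arms (15% or 20%), retention among exited patients r is 50% or 80%, 110 are randomised per arm, and exited patients are not analysed. With exit proportion e, retention among those who remain is (p − e·r)/(1 − e). Equal exits of 5% give equal remaining rates and a type I error of 5.0%.

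For exits of 10% in one arm and 5% in the other (99 and 104.5 patients remain):

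| p | r | Remaining rate, 10% exits | Remaining rate, 5% exits | Spurious difference | Type I error |
|---|---|---|---|---|---|
| 15% | 50% | 11.1% | 13.2% | −2.0 points | 7.2% |
| 15% | 80% | 7.8% | 11.6% | −3.8 points | 14.8% |
| 20% | 50% | 16.7% | 18.4% | −1.8 points | 6.2% |
| 20% | 80% | 13.3% | 16.8% | −3.5 points | 10.6% |

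First row: (0.15 − 0.10·0.50)/0.90 = 0.1111 and (0.15 − 0.05·0.50)/0.95 = 0.1316. The type I error is Φ((−1.96·se0 − d)/se1) + 1 − Φ((1.96·se0 − d)/se1), where d is the spurious difference, se0 the pooled and se1 the unpooled standard error. With d = −0.0205, se0 = 0.0458 and se1 = 0.0457, this is 0.0646 + 0.0079 = 0.0725.

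Exits of 15% against 5% give 10.6% to 56.3%. The upper end needs 0.15·0.80/0.15 = 80% of all retention in one arm to fall in exited patients, so I give it no weight.

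**4. Numbers under later randomisation.** If 5–10% meet an intraoperative criterion (assumed), randomising 220 after surgery needs 220/0.95 = 231.6, so 232, to 220/0.90 = 244.4, so 245, patients consented and operated on. If instead 220 are operated on and such patients are not analysed, 209 to 198 remain whichever order is used.

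**The case against.** The strongest reply is that no bias has been shown. Exits tied to prognosis distort the comparison only if they differ by arm, and the article gives no sign that they would; equal exits leave the type I error at 5.0%. The first criterion is mostly a list of named, verifiable procedures that a catheter-removal date is unlikely to change. The second uses a named grading standard, so meaningful discretion is confined to that grading. Central randomisation, the request to limit cointerventions and independent assessors also count for the trial. All of this stands, and it limits the point to a risk. The safeguards, however, do not cover exits decided in theatre.

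A reader might also infer several stronger things that the article does not support:

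- **That surgeons decide the exits.** No section says who does. It is a reasonable inference for nerve damage and added procedures, but still an inference.
- **That the nerve-damage exit depends on the outcome.** It is a prognostic factor recorded before any retention can occur.
- **That exited patients are lost from the analysis.** Statistical analysis states intention-to-treat and excludes only serious perioperative complications. It does not name the two intraoperative criteria. If these patients are analysed, selective loss does not arise and only arm-aware conduct of the operation remains.
- **That patients or power are wasted.** Power is 83.8% with 110 per arm and 79.8% with 99, but the same number operated on leaves the same number analysable in either order, and a 10% dropout allowance is already built in.
- **That the change is free.** Trial status says the trial began in July 2017 and is still recruiting, so a change now mixes two randomisation times.

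**Conclusion.** The point holds as a cheap, worthwhile design improvement, not as evidence of a biased trial. On the natural reading, allocation is revealed before resection without need, two exit criteria are determined after it, and the stated impossibility of blinding operating surgeons is a consequence of that timing.

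The size of any bias cannot be computed. Under the stated assumptions, exits of 10% against 5% would produce a spurious difference of 1.8 to 3.8 points, against a planned difference of 15, and a type I error of 6.2% to 14.8%; with equal exits there is none. These figures assume that exited patients leave the analysis and that retention is concentrated among them. The conclusion about timing needs neither assumption. An analysis plan could settle how exited patients are analysed, but it could not undo knowledge of the arm during surgery.

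**What to change.** For patients not yet randomised:

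1. In Grouping, place the web randomisation after surgery, once the two intraoperative criteria have been checked and before the day-2 removal.
2. Move additional pelvic surgery and Sugihara type IV nerve damage from Exit criteria to exclusions applied before randomisation.
3. In Randomization and blinding, state that surgeons are unaware of the allocation during the operation.

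Analyse patients already randomised as randomised. Report results separately for before and after the change as well as together, because the two periods define the population slightly differently: earlier patients who met an intraoperative criterion are in the randomised set, and later ones are not.

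**Cost.** One amendment moving a web log-in, a mixed randomisation time to describe, and more patients consented and operated on. The total is about 232–245 if all 220 were randomised under the new rule with 5–10% meeting a criterion (assumed), and fewer in practice because some are already enrolled. Catheter management does not change.

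**Not covered.** Postoperative Clavien–Dindo exits and the exclusion of serious perioperative complications in Statistical analysis can still fall after allocation and need separate repair.
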